## Objectives {7}

Therefore, this study protocol describes the design of an RCT comparing the efficacy of Sense for Kids therapy and dose-matched motor therapy to improve sensorimotor upper limb function in children and adolescents with uCP, who present with tactile impairments in the more impaired upper limb. The primary objective is to investigate if somatosensory discrimination therapy results in better bimanual performance at 6 months follow-up, compared to upper limb motor therapy. Secondly, we will investigate if somatosensory discrimination therapy is superior to improve somatosensory impairments. Lastly, we will explore the potential role of behavioral and neurological predictors of therapy response. The results of this study may aid in the selection of the most effective therapy intervention, specifically for children and adolescents with uCP who present with tactile impairments in the upper limb.

We hypothesize that somatosensory discrimination therapy will result in equal improvements in bimanual performance compared to upper limb motor therapy, immediately after the intervention period. However, we expect further improvements in bimanual performance during the follow-up period for participants who received somatosensory discrimination therapy because of the improved upper limb use in daily life, but not after upper limb motor therapy. We further hypothesize larger improvements in proprioceptive function and tactile perception, both immediately after the intervention and at follow-up, in participants who received somatosensory discrimination therapy. By considering the content and organization of the somatosensory discrimination therapy, we expect a higher therapy response for children and adolescents with worse somatosensory function and better attentional functioning at baseline. Lastly, we hypothesize that the occurrence of thalamic lesions is an important predictor of therapy response, because of the crucial role this brain structure has in the processing of somatosensory information that is transmitted from the periphery to the cortex [52].

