### Sample size {14}

The sample size calculation is based on the primary objective, which is defined as the retention of therapy effects on the primary outcome measure being bimanual performance measured with the Assisting Hand Assessment (AHA) at 6 months follow-up. The smallest detectable difference has been reported to be 5 AHA units [62]. Based on a previous intervention study in children with uCP [46], a standard deviation of 5.5 AHA units for improvements after intensive upper limb therapy was calculated by taking the average of the standard deviations between baseline and post-intervention and baseline and follow-up of both intensive therapy groups. The sample size estimate was calculated with G*Power for the following statistical test “Means: Difference between two independent means (two groups)” [63, 64]. With an estimated difference of 5 AHA units in the mean improvement between the intervention and control group and a standard deviation of 5.5 AHA units for both groups, an effect size of 0.9 was calculated. Based on an effect size of 0.9, an alpha level of 0.05 and a statistical power of 0.80, a sample size of at least 21 participants is needed in each group to detect a difference equal to or larger than the smallest detectable difference of 5 AHA units between groups. This number will be increased to 25 per group to account for inevitable dropouts and to maximize the study sample for prediction purposes.

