## Statistical methods

### Statistical methods for primary and secondary outcomes {20a}

All observations will be summarized as mean and standard deviation or median and interquartile range, according to the nature of the data. Baseline comparability between groups will be visually checked based on descriptive statistics. As the participants will be randomized to the intervention or control group, statistical testing of baseline differences will not be performed [108]. To study the time effects of the intervention and to allow for comparison between both groups, linear or generalized mixed models will be applied for the primary and secondary outcome measures. By using random effects, such models correct for the relation among repeated observations within subjects. An additional benefit of these models is that they provide a valid inference for missing values that are (completely) at random [109]. In case the data of an outcome measure is not normally distributed based on the Shapiro–Wilk test and/or visual inspection of the data distribution, transformations will be applied. The main endpoint will be to investigate if there is a difference in evolution of the AHA score over time between both groups. As such, interactions between therapy and time will be analyzed to test for differences in improvements over time between both groups (time*group interaction effect). When a significant interaction is identified, time trends will be tested in both therapy groups separately (time-effect). When the interaction is not significant, the main effect of time will be explored. Effect sizes for the full models will be further calculated using the Cohen’s partial η^2^ formula [partial η^2^ = (F × df_between_)/((F × df_between_) + df_within_)] [110]. Significant time trends will be further investigated with pairwise post hoc tests to compare individual time points (*T*_0_–*T*_1_, *T*_1_–*T*_2_, *T*_0_–*T*_2_). For the model of the primary outcome measure, the post hoc analysis will be Bonferroni corrected and the pairwise post hoc test for *T*_0_–*T*_2_ will be the primary outcome. For the models of secondary outcome measures, a false discovery rate with an adjusted *p*-value of 0.05 will be implemented. Effect sizes of these comparisons will be calculated using Cohen’s d formula [111]. For the second research objective, we will investigate predictive factors of therapy response. Both behavioral and neurological characteristics, i.e., somatosensory function at baseline, attentional functioning, and thalamic volume, will be included as covariates in the model for the primary outcome measure. All statistical analyses will be performed in SPSS Statistics for Windows. Level of significance will be set at 0.05, two-sided. When needed, adapted statistical techniques will be applied in close collaboration with Leuven Biostatistics and statistical Bioinformatics Centre (L-BioStat).

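### The T0–T2 post hoc test labelled primary compares visits, not therapies, and competes with the time-by-group interaction as the primary test

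*Protocol article*

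**What the plan says.** Objectives {7} sets a between-group aim at six months: to "investigate if somatosensory discrimination therapy results in better bimanual performance at 6 months follow-up, compared to upper limb motor therapy". Sample size {14} is built on the same quantity: "With an estimated difference of 5 AHA units in the mean improvement between the intervention and control group", with an SD of 5.5, using a test for two independent means.

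Statistical methods {20a} starts in line with this: "The main endpoint will be to investigate if there is a difference in evolution of the AHA score over time between both groups". The tool is the mixed model, in which "interactions between therapy and time will be analyzed to test for differences in improvements over time between both groups (time*group interaction effect") is assessed. The section then branches:

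- If the interaction is significant: "When a significant interaction is identified, time trends will be tested in both therapy groups separately (time-effect").
- If it is not: "When the interaction is not significant, the main effect of time will be explored".
- After either branch: "Significant time trends will be further investigated with pairwise post hoc tests to compare individual time points", the pairs being T0–T1, T1–T2 and T0–T2.

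For the AHA model these post hoc tests are Bonferroni-corrected, and the T0–T2 pairwise test is designated the primary outcome. Table 1 under Outcomes {12} lists the primary AHA outcome at T0 and T2, and the AHA at T0 and T1 as a separate secondary row.

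**The concern.** One section gives primary status to two different tests. The second, which carries the explicit label, is reached only after the plan has moved to time trends within each arm or over both arms. A T0–T2 comparison made there answers whether children changed between baseline and six months. It does not answer whether one therapy led to a larger change than the other.

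This matters because both arms receive 18 hours of active therapy, and Objectives {7} expects equal improvement in both by T1. A within-arm gain at six months is therefore compatible with no difference between therapies. The interaction is the only between-group test described. If it spans three visits, it can be significant because of a difference at T1 that has gone by T2, and the T0–T2 test that follows would not reveal this.

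**Working it through.** **Inputs.** From Sample size {14}: difference 5 AHA units, SD of change 5.5, d = 0.9, power 0.80, 21 per group raised to 25. From Statistical methods {20a}: two-sided 0.05 and three post hoc pairs, hence a Bonferroni level of 0.05/3 = 0.0167. Assumptions, because the protocol gives no figures: the gain in each arm, and compound symmetry over three visits.

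**1. The plan's own figure.** Two-sample t-test, noncentral t, ncp = d·√(n/2). With d = 0.9 and n = 21, ncp = 0.9 × √10.5 = 2.92 on 40 df, and power is 0.812. The stated 21 per group reproduces, for a between-group test at two-sided 0.05.

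**2. What the labelled test compares.**

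| Interaction | Next step | T0–T2 test then compares |
|---|---|---|
| Significant | Time effect in each arm | T0 with T2 within one arm |
| Not significant | Main effect of time | T0 with T2 over both arms |

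Neither row is the quantity sized in step 1.

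**3. Whether the interaction isolates six months.** With T0, T1 and T2 in the model it has 2 df. Under compound symmetry the residual variance is 5.5²/2 = 15.125, and ncp = (n/2) × Σ(δt − δ̄)² / 15.125, where δt is the between-arm difference at visit t.

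- Difference at T1 only, δ = (0, 5, 0): Σ(δt − δ̄)² = 25 − 25/3 = 16.67, so ncp = 11.6 (n = 21) or 13.8 (n = 25). Power is 0.86 or 0.92.
- Difference at T2 only, δ = (0, 0, 5): the sum is the same, so the ncp and power are the same.

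The omnibus test is thus equally likely to be significant for a difference confined to T1 as for one confined to T2.

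**4. The full sequence when the arms differ at T1 only.** Simulated with gains of (0, 0, 5) in the experimental arm and (0, 5, 5) in the control arm; exchanging the arms gives the same rates.

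| | 21 per arm | 25 per arm |
|---|---|---|
| Interaction significant | 86% | 92% |
| Followed by a significant within-arm T0–T2 test in the experimental arm (0.0167) | 80% | 89% |
| Between-group T0–T2 contrast significant (0.05) | 5% | 5% |

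The last row is the nominal error rate, as it should be with no difference at T2.

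**5. Identical therapies.** The interaction is significant in about 5% of trials. With a 3-unit gain in both arms and 25 per arm, the interaction is significant and exactly one arm then shows a significant T0–T2 change in about 4%. In the remaining 95% or so, the test labelled primary is the pooled pre-post test.

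**6. Power of the contrast that the objective needs (d = 0.9).**

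| Level | 21 per arm | 25 per arm |
|---|---|---|
| 0.05 | 0.81 | 0.88 |
| 0.0167 | 0.66 | 0.76 |

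At 0.0167, 28 per arm would be needed for 0.80.

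**The case against.** The best defence is that the plan does test the groups against each other. It calls the difference in AHA evolution the main endpoint, tests it by the interaction, and looks within arms only once that test is significant. This stands, and it rules out some stronger readings.

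- A reader might infer that the analysis has no group comparison. It has one, the interaction.
- A reader might infer a very high false-positive rate for superiority. With 25 per arm and a 5-unit gain in both arms, both within-arm tests are significant in 94% of trials; with a 3-unit gain, exactly one is in 49%. Those rates ignore the gate. With it they fall to about 4% each.
- The pooled test is significant in more than 99.9% of trials when both arms gain 5 units. That is not a false-superiority rate: this branch follows a non-significant group comparison, and the plan does not say a pooled time effect will be read as superiority. Nor does it say that significance in one arm only will be.

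The 2 df are also an inference. Table 1 lists T0 and T2 alone for the primary outcome, and in a two-visit model the interaction would be exactly the wanted 1-df contrast. The three post hoc pairs favour the three-visit reading, but the text does not settle it.

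Finally, the T1-only pattern runs against the trial's hypothesis of equality at T1 and divergence later. Under the hypothesised pattern the omnibus test loses no power against the single contrast (about 0.86 against 0.82 at 21 per arm, with a 5-unit difference). The T1-only case is a stress test, not a forecast.

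The authors may have meant a T0–T2 interaction contrast. The text does not say so: its post hoc tests compare time points after a time trend.

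**Conclusion.** The point holds as a contradiction over which test is primary. The T0–T2 test that carries the label is a within-arm or pooled change, whereas the objective and the sample size concern the between-group difference in that change. The interaction does not resolve this if three visits are modelled. With a 5-unit difference at T1 only, it is significant in 86% to 92% of trials although the arms are equal at six months. Those percentages rest on a change SD of 5.5, compound symmetry and the assumed gains; the contradiction in the wording rests on none of them. With identical therapies the gate limits the inferential risk to about 5%, and what remains is a primary test that does not address the objective. The sample size is not at fault. Because this decides which result carries the trial's claim, it should be settled before the analysis.

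**What to change.** Name one primary analysis: the between-group difference in AHA change from T0 to T2, estimated as a 1-df group-by-time contrast from the mixed model, reported with its 95% CI and tested two-sided at 0.05. State that it is tested whatever the omnibus interaction shows and that it lies outside the Bonferroni set. Make the T0–T1 between-group contrast secondary and the within-arm changes descriptive. Say which visits enter the primary model, so that Table 1 and {20a} agree.

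The level must be stated explicitly, because keeping the three-fold correction on this contrast would take power below the planned 0.80 even with 25 per arm. The cost is one paragraph of analysis text, with no added participants or data. Trial status gives recruitment as open until as late as June 2027, and item {25} provides the amendment route.

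### The only effect size explicitly tied to the between-arm result is a partial eta-squared that is unsigned, not visit-specific and has undefined denominator df; no between-arm effect on the sizing scale is clearly named

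*Protocol article*

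**What the plan says.** Under Statistical methods for primary and secondary outcomes {20a}, the arms are compared through the time-by-group interaction in linear or generalized mixed models with random effects. The same section continues: "Effect sizes for the full models will be further calculated using the Cohen’s partial η^2^ formula". The formula is printed there: F times the between df, divided by that product plus the within df.

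If the interaction is significant, time trends are tested in each arm separately; if not, the main effect of time is explored. Significant time trends lead to pairwise tests of time points (T0–T1, T1–T2, T0–T2), and Cohen's d is assigned to those comparisons. The T0–T2 pairwise test is called the primary outcome, without stating whether it is within or between arms. Testing is fixed by "Level of significance will be set at 0.05, two-sided".

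Sample size {14} works on a different scale: "With an estimated difference of 5 AHA units in the mean improvement between the intervention and control group", with "a standard deviation of 5.5 AHA units for both groups, an effect size of 0.9 was calculated". The trial is sized "to detect a difference equal to or larger than the smallest detectable difference of 5 AHA units between groups". Objectives {7} asks a directional question about one visit: whether somatosensory therapy gives better bimanual performance at 6 months. It expects equal improvement immediately after therapy.

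**The concern.** The effect measure does not match the question.

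- **Direction.** A partial eta-squared from a 2-df interaction is the same whichever arm does better.
- **Visit.** It does not say whether the arms differ at T1, at T2 or at both, although the hypothesis is specifically about divergence by T2.
- **Scale.** It is a proportion and cannot be read against 5 AHA units.
- **Definition.** The formula comes from fixed-effects ANOVA, which has one error df. In a mixed model the denominator df depends on the covariance structure, and the article fixes only that random effects are used. The formula also gives one value per F-test, and a model with time, group and their interaction has three, so an effect size for the full model has no single meaning.

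At stake is how the result can be read. The interaction test itself is unaffected, but the one effect size explicitly tied to it would not answer the primary objective.

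**Working it through.** **1. The plan's own figure.** Inputs from Sample size {14}: "Based on an effect size of 0.9, an alpha level of 0.05 and a statistical power of 0.80"; two-sided from {20a}. The standardised difference is 5/5.5 = 0.909, stated as 0.9. A two-sample t-test with the noncentral t gives 21 per group (power 0.812 at d = 0.9; 0.820 at d = 0.909). This agrees with "a sample size of at least 21 participants is needed in each group". At the planned 25 per group, power is 0.88. The sizing scale is therefore a signed between-arm difference in mean change.

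**2. Inputs for partial eta-squared.** n = 25 per arm (N = 50), three visits, complete data. The SD comes from "taking the average of the standard deviations between baseline and post-intervention and baseline and follow-up of both intensive therapy groups". Taking 5.5 for both T0–T1 and T0–T2 is an assumption, because the source is an average. The SD of T1–T2 change is not given; 5.5 is assumed first and then varied.

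**3. F at the planning values.** Let the between-arm differences at T0, T1, T2 be (0, 0, 5), with mean 5/3.
- Sum of squared deviations: 25 − 25/3 = 16.667.
- Interaction mean square: (25/2) × 16.667 / 2 = 104.17.
- Error mean square: 5.5²/2 = 15.125.
- F = 104.17/15.125 = 6.887, so 2F = 13.774.

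With all change SDs equal, the unstructured-covariance F is the same.

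**4. The printed formula.**
- Random intercept, df 2 × (50 − 2) = 96: 13.774/(13.774 + 96) = 0.125.
- Unstructured, df 50 − 2 = 48: 13.774/(13.774 + 48) = 0.223.
- Ratio: 109.774/61.774 = 1.78.

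In 20,000 simulated trials the median ratio was also 1.78 (5th to 95th percentile 1.49 to 2.24).

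**5. Direction and visit.** (0, 0, −5), (0, 5, 0) and (0, 5, 5) each give the same sum of squared deviations, 16.667. For example, 50 − 100/3 = 16.667 for the sustained pattern. All four patterns therefore give 0.125 or 0.223. The hypothesised result and its reverse cannot be told apart.

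**6. Sensitivity to the SD of T1–T2 change, s.** The random-intercept error mean square becomes (30.25 + 30.25 + s²)/6. For the unstructured model let c = (60.5 − s²)/2. Then F = 156.25 × 30.25/(30.25² − c²) for an effect at T2 only, and F = 312.5/(30.25 + c) for a sustained effect.

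| s (assumed) | eta², 96 df | T2 only: eta², 48 df | ratio | sustained: eta², 48 df | ratio |
|---|---|---|---|---|---|
| 3 | 0.158 | 0.439 | 2.78 | 0.189 | 1.20 |
| 4 | 0.145 | 0.319 | 2.20 | 0.199 | 1.37 |
| 5.5 | 0.125 | 0.223 | 1.78 | 0.223 | 1.78 |
| 7 | 0.106 | 0.183 | 1.72 | 0.266 | 2.50 |

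A T1-only effect gives the same values as T2-only throughout.

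**The case against.** The article says partial eta-squared is calculated in addition; it does not make it the headline result. Direction, timing and units can be seen elsewhere. Observations are summarised by mean and SD (or median and IQR), Table 1 defines the primary metric as change in the 0–100 AHA score, and after a significant interaction each arm's time course is tested and given a Cohen's d. If the T0–T2 test called primary is meant between arms, its d is already on the 0.9 scale. Any one fitted model has one interaction F and one denominator df, and a random intercept, the simplest reading of the text, gives 96 with complete data. The covariance structure and interval estimates may stand in an analysis plan that is not shown.

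Most of this stands, and it limits the point. A reader might infer that no AHA-unit result will be available. The documents do not support that: planned means and SDs allow a crude difference, and an analysis plan may name the model contrast. A reader might also infer that the measure always nearly doubles with the covariance structure, or that it always ignores timing. The first depends on two structures assumed here and on an SD the article does not give. The second is exact only with equal change SDs; otherwise, under unstructured covariance, sustained and single-visit effects give different values. Nor does Sample size {14} make 5 units a criterion of success; it is the smallest detectable difference, used for sizing.

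What the objection leaves untouched is that partial eta-squared is unsigned, does not identify the visit and cannot be compared with 5 units. The order of the sentences in {20a} ties Cohen's d to time-point comparisons within an arm or pooled over arms, so a between-arm d is at best one possible reading. If the within-arm reading is intended, whether the primary test compares the arms at all is a separate and larger question.

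**Conclusion.** The point holds as a poorly chosen and under-defined effect measure. It does not show that a between-arm difference will go unreported. The absence of sign and of visit information follows from the 2-df test and needs no covariance assumption. The size of the ambiguity does need assumptions: 0.125 against 0.223 rests on 25 per arm, complete data, every change SD equal to 5.5, and a choice between random intercept and unstructured covariance. Over assumed T1–T2 change SDs of 3 to 7 the ratio runs from about 1.2 to 2.8. The interaction test, its error rate, the sample size and the data collected are unaffected. What suffers is the ability to read the primary result against the directional 6-month objective and the 5 units behind the sample size.

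**What to change.** In {20a}, replace the partial eta-squared sentence with wording to this effect: the effect measure for the primary outcome is the model-based between-arm difference in T0–T2 change in AHA units with its 95% CI, and the T0–T1 difference is secondary; the estimate is read against the 5 AHA units used in Sample size {14}. If a standardised value is wanted, divide that difference by the SD of change, which is the scale behind d = 0.9. State in the same place whether the T0–T2 test called primary is within or between arms.

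Drop partial eta-squared, or keep it as a secondary descriptor that names the F-test it comes from and the denominator df.

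The cost is one changed sentence, that clarification and one extra contrast from the model already planned. No further data or participants are needed.

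### The named primary test (AHA, T0–T2) sits inside a Bonferroni-corrected set of post hoc tests, but the sample size assumes one uncorrected between-group test at 0.05

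*Protocol article*

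**What the plan says.** **Sample size {14}.** The calculation is tied to the primary objective, bimanual performance on the AHA at 6 months follow-up. The inputs, both in units of the scale, are: "With an estimated difference of 5 AHA units in the mean improvement between the intervention and control group and a standard deviation of 5.5 AHA". From these follows the standardised figure: "an effect size of 0.9 was calculated". The test is a G*Power comparison of two independent means. The result: "an alpha level of 0.05 and a statistical power of 0.80, a sample size of at least 21 participants is needed in each group". The number is raised to 25 per group for dropouts and for the prediction analyses. Multiplicity is not mentioned.

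**Statistical methods {20a}.** The main endpoint is a difference between groups in how the AHA evolves, tested through the time-by-group interaction in a mixed model. If the interaction is significant, time trends are tested in each group separately. If not, the main effect of time is explored. Significant time trends are followed by pairwise tests of T0–T1, T1–T2 and T0–T2. Then: "For the model of the primary outcome measure, the post hoc analysis will be Bonferroni corrected and the pairwise post hoc test for" T0–T2 is named as the primary outcome. The general level is also given: "Level of significance will be set at 0.05, two-sided". No adjusted level and no family size are stated, and T0–T2 is not exempted from the correction.

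**Objectives {7} and Table 1.** The primary objective is a between-group comparison at 6 months. Table 1 gives AHA change from T0 to T2 as the only primary outcome and lists the AHA at T1 as a secondary outcome.

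**The concern.** The same comparison is held to two different levels. {14} judges it at 0.05. {20a} puts it in a Bonferroni family, which with three members means 0.05/3 = 0.0167. If the correction is applied as written, the trial does not have the power that {14} states. The lost power also protects no primary claim, because there is one primary outcome at one time point and the T1 result is already secondary.

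There is a second difficulty. The sentence that names the primary test belongs to a run of tests that compare time points, whereas the objective and the sample size concern a difference between groups. A reader of {20a} alone cannot tell which test decides the trial.

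This could settle the result. A T0–T2 p-value between 0.0167 and 0.05 could be reported as positive or negative, depending on which section is followed.

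**Working it through.** **Inputs.** Difference 5 AHA units, SD of change 5.5 in both groups, effect size 0.9 (5/5.5 = 0.909, rounded), alpha 0.05, power 0.80, 21 per group raised to 25: all from {14}. Two-sided testing and the three listed pairs: from {20a}. The divisor of three is an inference from those pairs.

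**Method.** Two-sample t test with n per group: df = 2n − 2, noncentrality = d × √(n/2), critical value t(1 − alpha/2, df), power from the noncentral t distribution.

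**Step 1: reproduce the plan's figure.** With d = 0.9 and n = 21, df = 40 and noncentrality = 0.9 × √10.5 = 2.916. At two-sided 0.05 the critical value is 2.021 and power is 81.2%. With n = 20 power is 79.2%, so 21 is the smallest n that reaches 80%. The stated figure is correct for an uncorrected two-sided test. A one-sided test would need only 16.

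**Step 2: apply the correction.** At 0.05/3 = 0.0167 with n = 21, the noncentrality is unchanged, the critical value rises to 2.499 and power falls to 66.2%. With n = 25, df = 48, noncentrality = 0.9 × √12.5 = 3.182, the critical value is 2.481 and power is 75.6%.

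| Evaluable per group | d | Power at 0.05 | Power at 0.05/3 |
|---|---|---|---|
| 21 | 0.9 | 81.2% | 66.2% |
| 23 | 0.9 | 84.7% | 71.2% |
| 25 | 0.9 | 87.7% | 75.6% |
| 21 | 0.909 | 82.0% | 67.2% |
| 25 | 0.909 | 88.3% | 76.5% |

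Reaching 80% at 0.05/3 takes 28 evaluable per group (27 with d = 0.909), more than the 25 to be enrolled.

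**Step 3: closer to the planned model.** A simulation of 40,000 trials per setting tested the between-group T0–T2 contrast with the repeated-measures residual variance and its larger df. It assumed an SD of 5.5 for the change between every pair of time points. At 0.05/3, power was about 69% with 21 and 78% with 25 per group, still below 80%.

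**Step 4: the interaction test.** Under the same assumption, the 2-df interaction at 0.05 has these powers:

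- groups equal at T1 and 5 units apart at T2: about 86% with 21 and 92% with 25 per group;
- groups 2.5 units apart at T1 and 5 at T2: about 74% and 82%.

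If the T0–T2 contrast is tested at an uncorrected 0.05 but counts only after a significant interaction, power with 21 per group is about 79% in the first pattern and 73% in the second. Removing the correction alone therefore does not secure the stated power. The conditioning on the interaction has to go as well.

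**The case against.** The strongest reply is that 66% is the power of a test {20a} does not clearly describe. There, the between-group question is answered by the interaction, for which the only stated level is 0.05. The corrected pairwise tests come afterwards and compare time points, within each group or overall. Putting 0.05/3 on a two-sample test of change takes the level from one test and the effect size from another. On the pattern the protocol expects (equal at T1, divergence later), the interaction is adequately powered under the assumption in step 4. This stands, and it is why the power figures can only be conditional. It does not clear the plan: on the literal reading, the test named as primary is not the between-group comparison in {7} and {14}.

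Three further points stand in part:

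- **Divisor.** It is not stated. Three is the natural count. Testing the pairs within each group could make it six, and power with 21 per group would be about 56%.
- **Enrolment.** The target is 25 per group, so 66% is the low end of a range.
- **Direction of error.** Bonferroni does not inflate the type I error or bias the estimate; the cost is power.

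A separate analysis plan may settle the matter, but the conflict lies between two things this protocol states, so it is not an omission.

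A reader might infer that the trial's power simply is 66%, or that the sample size was miscalculated. The document supports neither. The arithmetic in {14} is right for the test it names, and 66% depends on the between-group reading, a divisor of three and only 21 evaluable per group.

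**Conclusion.** The protocol does not hold one consistent definition and level for its primary test. Taking T0–T2 as the between-group change contrast, a divisor of three and an effect size of 0.9, power is about 66% to 76% for 21 to 25 evaluable per group. Even with no dropout it misses the stated 80%. At the lower end, a true 5-unit benefit would be missed about one time in three, where {14} implies one in five. On the literal reading the shortfall cannot be put as a single figure, and the defect is instead that the named primary test may not be the one that was sized. Either way {20a} and {14} need to be brought into line before the data are analysed.

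**What to change.** State in {20a} that the single primary test is the between-group difference in AHA change from T0 to T2, estimated from the mixed model and tested at two-sided 0.05. Say explicitly that it is not conditional on the time-by-group interaction and lies outside the Bonferroni family. Make T0–T1, T1–T2 and the within-group time trends secondary. This matches {7}, {14} and Table 1, and on the t-test calculation gives about 81% power with 21 and 88% with 25 per group.

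If the correction is to stay on the primary test, state the divisor and restate the power in {14} as about 66% to 76% (for a divisor of three).

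The preferred change needs no extra participants, but it is more than an edit of wording. It alters the hierarchy of tests, so it should go through the amendment route in {25}. The price is that the interaction test and the other pairwise contrasts lose confirmatory standing.
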